## Monitoring

This pilot study will not have an independent Data and Safety Monitoring Board. Investigators will keep track of adverse events as they occur, and will revise the protocol and informed consent if an excess of adverse events is observed. Specifically, the trial will be put on hold (no new enrollments), revised, and resubmitted to the REB for approval before resuming, in any of the following circumstances:Two serious adverse events that are possibly related to study participation and that occur during the participant’s first week of the study, as serious adverse events are unlikely to be related to the study drugs after methadone or SROM have reached steady-state levels.Study drug-related adverse events requiring intervention (including but not limited to those meeting the criteria for serious adverse events) in 5 or more of the first 10 participants; 10 or more of the first 20 participants; 15 or more of the first 30 participants; or 20 or more of the first 40 participants.

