### Study setting

The opioid overdose crisis has disproportionately affected under-served communities, including those with low socioeconomic status and complex medical and mental health issues. This study will be conducted at the Hope to Health Research and Innovation Complex in Vancouver’s Downtown Eastside (DTES), a neighborhood of approximately 18,000 residents with high rates of poverty, homelessness, mental illness, and drug use [16]. Residents of the DTES are disproportionately impacted by the ongoing opioid overdose crisis: in 2023, the rate of overdose deaths per 100,000 population in the DTES was 560.9, which was ten times higher than in the rest of the city of Vancouver (56.7) or in the province of BC as a whole (46.5) [17].

Hope to Health is an integrated facility that includes a low-barrier interdisciplinary Primary Care Clinic which currently supports 2800 active clients, and a co-located Supervised Consumption Site. The Supervised Consumption Site handles approximately 1000 visits per month, of which 90% involve use of opioids with or without other substances. This is a nurse- and peer-led service offering safe spaces to use unregulated or prescribed substances, as well as distributing harm reduction supplies and offering nursing care and referrals to the Primary Care Clinic or other services, as needed. Both the Primary Care Clinic and the Supervised Consumption Site support a safer drug supply program that offers clients the possibility of replacing their unregulated drug supply with prescribed pharmaceutical grade alternatives, including hydromorphone tablets or fentanyl patches.

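### One possibly related death in a participant's first week does not by itself trigger the pre-specified enrolment hold, and the trial has no independent safety board

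*Protocol article*

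**What the plan says.** The Monitoring section states: "This pilot study will not have an independent Data and Safety Monitoring Board". Investigators follow adverse events themselves and revise the protocol if they see too many. The section then lists the circumstances in which "the trial will be put on hold (no new enrollments), revised, and resubmitted to the REB for approval before resuming". There are two:

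- **Count criterion:** "Two serious adverse events that are possibly related to study participation", where each falls within the first study week of the participant concerned. The reason given for the first-week window is that later serious events are unlikely to be caused by the study drugs once these have reached steady state.
- **Proportion criterion:** drug-related adverse events requiring intervention, serious ones included, "in 5 or more of the first 10 participants; 10 or more of the first 20 participants; 15 or more of the first 30 participants", and likewise 20 or more of the first 40.

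Neither criterion gives a fatal event separate weight. Elsewhere death appears as a secondary outcome (Study objectives, Secondary outcomes) and in the schedules of assessments at Day 7 and at 1, 3, 6 and 12 months. No trial-level action is attached to it. The section on treatment and study discontinuation deals with individual participants only.

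The Overview of study design gives the primary goal as finding unforeseen problems that affect participant safety. It justifies 50 participants by 92% confidence of identifying a problem with 5% prevalence.

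**The concern.** A possibly related death in the first week is the gravest signal this pilot could produce. Under the count criterion it is one event of the two required. Under the proportion criterion it adds one participant towards 5, 10, 15 or 20. On the written rule, therefore, it requires no halt to enrolment.

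The point carries weight here for three reasons. The investigators are the only monitors named. The article expects higher-than-standard starting doses and describes the first 7 days on methadone as the period of maximum risk. Recruitment is ongoing, so participants could be enrolled between a first death and a second serious event. A pre-specified hold exists so that such a decision need not rest on judgement made under pressure by those running the trial.

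**Working it through.** **Inputs.** From the article: n = 50; 5% prevalence and 92% confidence (Overview of study design); the two hold criteria (Monitoring); 560.9 overdose deaths per 100,000 in the Downtown Eastside in 2023 (Study setting). The article gives no expected rate of first-week death or serious adverse event, so the risks below are assumptions, shown over a range. At most one event per participant is assumed.

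**1. The plan's own figure.** P(at least one) = 1 − 0.95^50 = 1 − 0.077 = 0.923. This reproduces the stated 92% and shows that a single occurrence counts as identification.

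**2. Two occurrences at the same prevalence.** P(exactly one) = 50 × 0.05 × 0.95^49 = 0.202. P(at least two) = 0.923 − 0.202 = 0.721. So there is a 72% chance of meeting a two-event count, and a 20% chance of seeing exactly one event and not meeting it.

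**3. The same calculation over assumed fatal risks.**

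| Assumed risk of a possibly related first-week death | No death | Exactly one | Two or more |
|---|---|---|---|
| 0.5% | 77.8% | 19.6% | 2.6% |
| 1% | 60.5% | 30.6% | 8.9% |
| 2% | 36.4% | 37.2% | 26.4% |
| 5% | 7.7% | 20.2% | 72.1% |
| 10% | 0.5% | 2.9% | 96.6% |

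The middle column is the one that matters: a death has occurred, and the count criterion is unmet unless there is also a possibly related non-fatal serious event. At 2%, this is 37.2/63.6 = 58% of the trials with any death.

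**4. Is the proportion criterion a backstop?** The exact cumulative probability of crossing 5/10, 10/20, 15/30 or 20/40 is 0.006% at a 5% event rate, 0.16% at 10% and 3.4% at 20%. It is not a safeguard against rare events.

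**5. How often might a one-death trigger fire on background mortality?** At the neighbourhood rate, expected overdose deaths are 50 × (7/365.25) × 0.005609 = 0.0054, a chance of about 0.5%. If participants' risk is assumed ten times higher, the expectation is 0.054 and the chance is 1 − exp(−0.054) = about 5%. Both treat every background overdose death as judged possibly related.

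**The case against.** The strongest reply is that the listed circumstances are automatic triggers and do not oblige anyone to continue enrolling otherwise. Investigators follow events as they occur, and they or the REB may pause at any time. This stands. A reader might infer that enrolment would carry on after a death, or that a death would go unreviewed. The article says neither.

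A second reply is that this is a condensed article, and that handling of single fatal events may be set out in the full protocol. Reporting duties may well be there. But the article states the hold threshold explicitly and makes no exception for death, so the point concerns a rule as fixed, not a missing detail.

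A third reply concerns the figures. A reader might infer that, at a 2% fatal risk, the two-event rule misses the problem in 74% of trials (1 − 0.264). That would be unfair to the rule. It includes the 36% of trials with no death, where no rule could act, and it ignores non-fatal serious events, which also count. With all possibly related serious events together at 4%, 5% or 10%, the two-event count is reached in 60%, 72% or 97% of trials.

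Nor does the neighbourhood figure prove that a one-death trigger would almost never fire by chance. It covers all residents and overdose deaths only, whereas participants have opioid use disorder and a urine test positive for fentanyl. The ten-fold multiplier is an assumption.

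Finally, the two-event threshold was a deliberate choice in an REB-approved protocol and is defensible for non-fatal events. That defence does not carry over readily to a death.

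**Conclusion.** The point holds in a limited form. On the written criteria, one possibly related first-week death does not by itself trigger the hold. The exceptions are a death that is the second possibly related serious event, or one that brings the proportion criterion to its threshold. No other section of the article provides a trial-level pause. This conclusion rests on the text alone and on none of the assumed rates.

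It is a weakness in a stated design choice, not an arithmetic error: the 92% is correct. Nor is it a formal contradiction, since identifying a problem and halting for it are different acts. The two do fit badly together: the sample size is justified by a single occurrence, while the mandatory response needs two, even when the first is fatal. The size is illustrative, with exactly one death in about 31%, 37% and 20% of trials at assumed fatal risks of 1%, 2% and 5%. The change is a cheap and worthwhile improvement to participant safety.

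**What to change.** Add one item to the hold list in the Monitoring section: any single death in a participant's first week that is possibly related to study participation puts new enrolment on hold pending REB review. Keep the two-event criterion for non-fatal serious adverse events, and leave the proportion criterion unchanged. If the full protocol already provides for this, say so in the article's monitoring text.

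The cost is a protocol amendment during recruitment and a small chance of an unnecessary pause: about 0.5% at the neighbourhood overdose-death rate, about 5% if participants' risk is assumed ten times higher. The true background rate for this population is not given. A hold under the present wording also means revision and resubmission, so the new item should state whether REB review alone is enough to resume.

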## Current status of the study

The study protocol and informed consent form have received approval from the University of British Columbia/Providence Health Care Research Ethics Board (UBC/PHC REB Number H23-00111). The use of safe drug supply, opioid agonist therapy (OAT), and experimental approaches such as IV fentanyl for the treatment of severe opioid use disorder at the Hope to Health Research and Innovation Centre have been approved by Health Canada as part of its Substance Use and Addictions Program. Study recruitment is ongoing.

## Discussion

This is the first study to objectively estimate opioid tolerance and use it to determine individualized starting doses of oral OAT for use in an outpatient setting among people who use unregulated fentanyl. This study was initiated in response the inadequacy of current OAT dosing recommendations to address the increasing contamination of the unregulated drug supply with high-potency opioids, mainly fentanyl and its analogues, resulting in an ongoing crisis of opioid overdose and death in BC and elsewhere.

The SIFI procedure involves an IV induction with medical fentanyl, guided by pharmacological principles [33, 34], and has been implemented successfully in an in-hospital setting [3]. To optimize participant safety in this outpatient study, participants will be closely supervised in the clinic during and after the IV fentanyl induction procedure.

A limitation of the SIFI protocol is that sedation observed during the induction procedure may be due to other factors in addition to medically-administered IV fentanyl. In a setting where multi-substance use is common, other contributing factors may include prescription, non-prescription, or unregulated sedating substances (e.g. benzodiazepines, alcohol), and/or catecholamine depletion as a consequence of chronic use of methamphetamine or other stimulants. Operationally, any somnolence or lethargy observed during the induction procedure is attributed to the administered IV fentanyl. If additional sedating factors are present, the consequence would be to underestimate the participant’s opioid tolerance and administer too low a dose of methadone or SROM to fully meet their opioid requirements. This limitation is unavoidable in the interests of participant safety in a setting where the potential effects of concomitant sedating substances cannot be determined or quantified.

Another potentially confounding factor in the calculation of opioid tolerance could be the presence of buprenorphine, an opioid partial agonist that is sometimes prescribed for the treatment of OUD. While current use of either buprenorphine extended-release (Sublocade®) or buprenorphine-naloxone (Suboxone®) is exclusionary in our protocol, it should be noted that buprenorphine extended-release (Sublocade^®^) has a long terminal half-life and relevant plasma concentrations can be maintained for up to 5 months after the last administration [35, 36]. If the SIFI protocol were to be implemented in a setting where these agents are in regular use, it may be prudent to ensure a 5-month interval has passed since the last Sublocade^®^ dose or to ensure buprenorphine is absent during urine drug testing, to mitigate the confounding effects of residual buprenorphine on the assessment of opioid tolerance using IV fentanyl.

We expect that application of the SIFI protocol will result in higher-than-standard starting doses of oral OAT. Accordingly, in the interests of participant safety and to prevent early withdrawal after OAT initiation, every effort will be made to ensure the protocol-planned assessments are completed during the 3 h after the first dose of OAT and the first 7 days thereafter. Participants will be offered an honorarium for remaining in the clinic for a full day including participation in the induction and 3 h of assessment time following the first OAT dose. Honoraria will also be provided for participants returning to the study clinic for daily assessments during the first week on OAT.

We expect that the potential harms associated with IV fentanyl induction and high-dose methadone or SROM in this protocol will thus be minimized, especially when compared to the known harms associated with OAT dropout and continued use of the unregulated drug supply. We predict that tailored starting OAT doses will lead to therapeutic target levels being achieved more quickly, thereby more effectively managing opioid withdrawal and cravings, and in turn leading to increased retention on life-saving OAT and decreased reliance on the toxic street drug supply. We believe the findings of this study will be generalizable to other clinical settings, particularly in jurisdictions where fentanyl use is widespread.

## Data Availability

After the study is finished, results will be published in medical journals and reports, and presented at scientific meetings and conferences. These materials will be made available on the British Columbia Centre for Excellence website at www.bccfe.ca. Results will only be reported as aggregate data. No information which could identify any individual study participant will be included in any such presentations or publications. The final study dataset will be made available on specific written request to the Principal Investigator. The required study data will be de-identified and only the unique study code will be used for individual participant data.

## Abbreviations

BC: British Columbia
COWS: Clinical Opiate Withdrawal Scale
ECG: Electrocardiogram
EMR: Electronic medical record
IV: Intravenous
MSQ: Medication Satisfaction Questionnaire
OAT: Opioid agonist therapy
OT: Opioid tolerance
OUD: Opioid use disorder
POSS: Pasero Opioid-induced Sedation Scale
SIFI: Symptom-inhibiting fentanyl induction
SROM: Sustained-release oral morphine
TdP: Torsades de Pointes
UDT: Urine drug test
